**Table 1 T1:** **Neurological**, **neuropsychological and psychiatric examination**

**Neurological examination**:	Sensory and motor systems
**Neuropsychological Pain Evaluation**:	Coping skills and personality assessment
**Neuropsychological Cognitive Assessment and Psychiatric Evaluation**:	a) California Verbal Learning Test
	b) Wechsler memory Scale
	c) Delis-Kaplan Executive Function System
	d) Wisconsin Card Sorting Test
	e) Beck Depression Inventory
	f) Beck Anxiety Inventory
	g) Columbia Suicide Severity Rating Scale (CSSRS)
	h) Montgomery-Asburg Depression Rating Scale (MADRS)
	i) Twenty Item Positive and Negative Affect Schedule (PANAS) and NEO Five Factor Inventory (NEO_FFI)

Neurological, neuropsychological pain and neuropsychological cognitive and psychiatric examinations; marked by an asterisk in Figure 1, these examinations will be conducted at pre-operative baseline, at the time of randomization and at month 12 and 24 following randomization (well into phase VI follow-up testing).

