#### Phase II: pre-operative baseline evaluation

Phase II, or pre-operative baseline evaluation (Figure 1), involves collection of several clinical outcome measures, including extensive neurological, neuropsychological pain and cognitive and psychiatric assessments (Figure 1, Table 1). These assessments are performed before implantation, and repeated during the randomized phase, and again during the open-label follow-up phase. These evaluations are conducted by the same specialized team that routinely assesses neurologic, neuropsychological, cognitive and neuropsychiatric function in our clinical program and in our research studies in DBS. Patients also undergo functional neuroimaging (Figure 1).

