**Figure 1 F1:**
[figure not shown]
**Study design.** Flowchart of the study design based on specified CONSORT clinical trial guidelines [23]. Categories defined in CONSORT guidelines are marked on the right margin of the figure. ^*^Time points when neurological, neuropsychological pain or neuropsychological cognitive evaluations (Table 1) will be conducted. During phase V, fMRI and MEG evaluations will be conducted at 2 and 5 months after randomized intervention allocation. During the open-label phase, follow-up assessments are conducted at month 9, 12, 18 and 24 for outcomes listed above and at month 12 and 24 for fMRI and MEG. TPS, thalamic pain syndrome; DBS, deep brain stimulation; fMRI: functional magnetic resonance imaging; MEG: magneto-encephalography; EuroQOL (EQ-5D), Euro Quality of Life scale.

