### Endpoints of safety

Risks can be related to the procedures for implantation of DBS hardware, or the stimulation of the target area. Additional risks could be related to conducting MRI with implanted DBS. Events or instances that can present as risks are noted in detail in Table 2. Clinical experience of the research team, pre-operative image guidance, prophylactic antibiotics, and preparatory laboratory work is critical in mitigating risks related to DBS and implantation. Risks of stimulation are mitigated by choosing settings below the threshold for intolerable side effects [19]. Risk for suicidal ideation is monitored throughout the trial using C-SSRS. The protocol is outlined such that if serious signs are detected, psychiatric assessment will promptly follow. If the risk remains high for more than 28 days or if two or more events of imminent risk are recorded, then the individual will be removed from the blinded phase of the study.

**Table 2 T2:** Overall risks of the study across various categories

**Category of Risks**	**Specific Risks**
**Risks of DBS surgery and Implantation of Pulse Generator**	Intracerebral hemorrhage; infection abscess; meningitis; misplacement of leads requiring revisions; post-operative displacement of leads; reaction to lead materials; hypodensity with mass effect around lead; intracranial extra-axial hemorrhage; stroke; pain at site of surgery; migration of leads; erosion of skin over hardware; hardware problems, such as abnormal impedances; hydrocephalus; seizures/epilepsy; cerebrospinal fluid leak; seroma; collection formation; pneumothorax/hemothorax/pleural effusions due to IPG; injury along the tunneling trajectory in the region of head, neck or chest; risks related to anesthesia (severe injury, cognitive decline, and death)
**Risks Pertaining to Hardware Maintenance**	Migration; infection; hardware malfunction/break; insulation problems; leaks of electricity; reaction to implants; erosion; incompatibility with MRIs; incompatibility with surgical equipment, medical devices or diagnostic devices

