#### Sample size estimation and efficacy

Since the study is designed as a randomized, sham-controlled, double-blinded study, we will also be able to evaluate whether any potential trend indicates efficacy, which would help compute effect sizes and variance in DBS versus sham phases to estimate sample sizes for adequate power in future. Our within-subject, crossover design would also yield the magnitude of placebo effect related to the surgical process itself that is an important practical issue to consider in effect-size estimates for the future.

This study was initially planned to involve a total of 34 patients. The sample size was estimated based on changes in PDI in patients with central pain syndrome in an earlier study [37]. It was determined that to detect an effect size of 0.5 (equivalent to a 7-point decrease in PDI), a total of 34 patients would need to have been included for statistical power of 80% on a two-sided test with a type I error probability of 0.05. The Food and Drug Administration of the United States has, however, determined in its review that the study should initially enroll 10 patients as part of a phase I, safety study.

Due to the small sample size of the proposed pilot phase I trial, procedures for corrections for multiple comparisons cannot be instated; the scope of the subsequent phase II trial would be better suited to include such procedures. By examining only a priori hypotheses, we aim to mitigate the probability of making type I errors. Therefore, we will compare the differences in the primary and secondary outcomes in the third month of DBS with those in the third month of sham stimulation using the paired *t*-test at α = 0.05. Despite the sample size limitation, we expect the study to be informative in estimating the magnitude of the placebo effect after DBS for pain, as well as variances in outcome that to date are unknown. These will be valuable in designing subsequent phase II and III studies.

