Despite the inclusion of a placebo-controlled phase, altogether, patient expectations from undergoing a clinical-like investigational DBS procedure, therapeutic confusion within the investigative team, and unintentional cues during programming, can introduce several unwanted influences in clinical trial design. By introducing blinding for patients and employing a team where the investigator collecting outcome data is blinded and the surgeon and programming physicians are unaware of outcomes during the blinded phase, we aim to minimize unintentional cues and ensure investigator equipoise [22]. We are also minimizing unintentional cues by allowing adequate time (approximately 1 month) to elapse between programming for DBS and randomization to the intervention group, so that memory of the experience of stimulation is reduced. Nevertheless, a caveat exists. The therapeutic effects may influence patients’ perceptions, and thus, the integrity of experimental blinding [42]. For instance, early effects on mood and anxiety may inflate perceived benefits. To study this possibility, we will document the frequency with which patients can guess the allocated treatment and we will relate the Beck depression and anxiety inventories with PDI to note whether the placebo of DBS confounds therapeutic differences from the sham. We acknowledge, however, that small sample size may limit our ability to draw concrete inferences.

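### The Table 1 note schedules the mood, suicidality and cognitive scales at no visit between randomization and month 12, contradicting three other sections on blinded-phase assessment

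*Protocol article*

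**What the plan says.** The Table 1 note fixes the times for the whole table: "these examinations will be conducted at pre-operative baseline, at the time of randomization and at month 12 and 24 following randomization". The lettered items a to i name ten instruments: four cognitive tests, BDI, BAI, C-SSRS (listed as "Columbia Suicide Severity Rating Scale (CSSRS"), MADRS, PANAS and NEO-FFI.

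Other sections of the article speak to the same assessments:

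- **Phase II: pre-operative baseline evaluation**, citing Figure 1 and Table 1: "These assessments are performed before implantation, and repeated during the randomized phase, and again during the open-label follow-up phase".
- **Endpoints of safety**: "Risk for suicidal ideation is monitored throughout the trial using C-SSRS". The same paragraph removes a patient from the blinded phase on this condition: "If the risk remains high for more than 28 days or if two or more events of imminent risk are recorded".
- **Discussion and conclusions**: "we will relate the Beck depression and anxiety inventories with PDI". The stated purpose is to see whether a placebo response confounds the difference between DBS and sham.
- **Sample size estimation and efficacy**: the plan will "compare the differences in the primary and secondary outcomes in the third month of DBS" with those in the third month of sham, by paired t-test.
- **Figure 1 caption**, on the open-label phase: "follow-up assessments are conducted at month 9, 12, 18 and 24 for outcomes listed above".

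**The concern.** A scale can inform a DBS-versus-sham contrast only if it is measured while patients are on each blinded condition. The Table 1 note, read as written, gives no such measurement for any scale in the table. The later visits, at months 12 and 24, are open-label with everyone on active stimulation, so they cannot supply a sham value.

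Two things are at stake. The first is the planned check on whether mood and anxiety effects, or a placebo response, explain a PDI difference. The article presents this as its way of studying a recognised threat to blinding. The second is suicidality monitoring. The blinded-phase removal rule needs repeated risk assessments within six months, and the only visit-level schedule given for C-SSRS has none there. A site following the note and a site following the safety section would collect different data.

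**Working it through.** The plan has no computed figure on this point. The check places the stated visits on the trial's time axis and compares the sections.

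**Inputs**

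- Time zero is randomization; the Table 1 note counts months 12 and 24 from it.
- Crossover comes 3 months after randomization (Discussion and conclusions).
- The open-label phase starts when the third month after crossover is complete (Phase VI), so the blinded phase ends at 3 + 3 = 6 months.
- Table 1 visits: pre-operative baseline (before time zero), month 0, month 12, month 24.

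**Placement**

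| Interval | Condition | Table 1 visits |
|---|---|---|
| Up to and including month 0 | before blinded treatment | baseline, randomization |
| After month 0, to month 3 | first blinded period | none |
| After month 3, to month 6 | second blinded period | none |
| After month 6 | open-label, no sham | months 12 and 24 |

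Visits after allocation within the blinded phase: 0. Gap from randomization to the next visit: 12 − 0 = 12 months, of which 6 are blinded and 12 − 6 = 6 are open-label.

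**Consequence for each use, if the note is followed**

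1. *BDI and BAI against PDI.* This needs both inventories under DBS and under sham. The note gives none under either, so the analysis cannot be run.
2. *C-SSRS.* The removal rule turns on high risk lasting more than 28 days, or on two recorded events of imminent risk. Visits 12 months apart cannot show either within the blinded phase. Table 2 also bases suicidality on items from MADRS, C-SSRS and BDI plus a behavioral interview; all three scales are in Table 1.
3. *Repetition in the randomized phase.* The Phase II statement is contradicted unless the randomization visit itself counts as a repeat. That visit precedes any blinded treatment effect.
4. *Third-month paired t-test.* The test is stated for primary and secondary outcomes. PDI and the VAS are not in Table 1, so the note does not touch them. Whether the test covers the Table 1 scales is unclear. The section Secondary endpoints numbers three endpoints and then introduces these scales as other outcomes. Yet two of the three are fixed at 2 years and the third is a yes/no answer, so none suits a third-month paired t-test as written. That makes a wider meaning plausible, but it remains an inference.

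**The case against.** The strongest reply is that one note should not override the rest of the article. Phase II and Endpoints of safety both state collection that reaches into the blinded phase, and Outcomes of efficacy says depression, anxiety and suicidal ideation are recorded at several times shown in Figure 1. That figure is not available here and may carry the right visits. Its caption also describes the asterisked examinations without naming the psychiatric ones, whereas the Table 1 note includes them, so the four-visit schedule may not be meant for the mood and suicidality scales. C-SSRS safety checks may run apart from the full battery, and a condensed article need not print every safety visit.

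Much of this stands. A reader might infer that the trial will have no blinded-phase data on mood or suicidality; the documents do not support that, because other sections say such data are collected. A reader might infer that the third-month comparison as a whole is lost; it is not, since PDI and the VAS lie outside Table 1 and the test is not clearly planned for the scales inside it. A reader might also infer that the hypothesis about affect and disability becomes untestable. But disability is measured by PDI, the McGill questionnaire has an affective category and is not in Table 1, and imaging is scheduled at months 2 and 5.

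What does not stand is that nothing needs correcting. Reading the randomization visit as the whole randomized phase is strained, because the same sentence uses randomization as the origin for months 12 and 24. If Figure 1 shows more visits, the note contradicts the figure as well. Nor is this a detail left to the full protocol: the article states a schedule, and it conflicts with the article's own analysis and safety text.

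**Conclusion.** The point holds as an internal contradiction. The Table 1 note places ten instruments at four visits, with 0 of them after allocation within the 6 blinded months. That conflicts with Phase II, with Endpoints of safety, and with the BDI/BAI analysis in the Discussion. If followed, it would defeat that analysis and leave 12 months after randomization with no scheduled C-SSRS.

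This rests on reading the note literally and on the text alone, without the Figure 1 graphic. It does not show that blinded-phase data will be absent, and it does not affect the primary PDI comparison. It still needs correcting, because the two descriptions cannot both be carried out and the note is the most specific statement of timing for these scales.

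**What to change.** 1. Correct the Table 1 note so that at least BDI and BAI are taken in the third month of each blinded period (months 3 and 6), together with PDI and before stimulation is reprogrammed. Add MADRS if a DBS-versus-sham contrast on it is intended.
2. In Sample size estimation and efficacy, state whether the secondary outcomes include the Table 1 scales. Leave out of the third-month comparison any scale not measured then; the long cognitive battery could stay at its four visits on that basis.
3. Reconcile the C-SSRS timing in the Table 1 note with Endpoints of safety, including the removal rule, so that one schedule governs. Which timing is right is for the sponsor and investigators to settle.

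The cost is a schedule correction and a few short questionnaires at third-month assessments that the PDI comparison already requires.

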#### Phase III DBS implantation

All enrolled patients receive DBS implantation bilaterally in the VS/ALIC target. DBS lead implantation is completed in the same fashion as previously described by our group, but for the VS/ALIC target [18,24]. The VS/ALIC is targeted approximately at its junction with the anterior commissure and the electrodes are advanced further ventrally along the trajectory towards the VS. Once inserted, intraoperative testing with macrostimulation through the DBS lead is performed. Based on prior experience [20], we have noted that the most ventral electrode contacts elicit acute changes in mood or anxiety. At this stage, it is unknown if stimulation also produces changes in pain perception. If no effects are seen, the implanting team may consider revising the location of the lead(s). Once a location is identified, DBS leads are anchored to the skull and surgical sites are closed. The implantable pulse generator (IPG) is positioned in the infraclavicular area and connected to DBS leads under general anesthesia. Since the surgical intervention and general anesthesia may be a risk for cognitive decline, we serially assess cognitive function to note whether any patients experience negative effects on cognition related to our interventions (see Table 1).

#### Phase IV: DBS programming and titration

DBS programming is initiated at least a month after DBS surgery to allow for resolution of microlesional effects. In acute programming, patients are asked to report changes in mood, anxiety, pain or suffering with activation of one or more electrode contacts. If the affective reporting of pain is not influenced, then settings affecting mood and anxiety can be chosen for chronic stimulation. All stimulation settings are planned below a charge density of 30 μC/cm^2^/phase, using the formula:

$$\begin{array}{c} \text{Charge}\;\text{density}\;\left({\mathrm{\mu C}/\mathrm{cm}}^{2}/\text{phase}\right)\\ =\frac{\text{Voltage}\;\left(V\right)*\text{Pulse}\;\text{width}\;\left(\mathrm{\mu s}\right)}{\text{Lead}\;\text{surface}\;\text{area}\;\left({\mathrm{cm}}^{2}\right)*\text{Impedance}\;\left(Ω\right)}\;\mathrm{Eq}.\;1 \end{array}$$

#### Phase V: randomization and intervention

Once optimal settings are determined, stimulation is turned off for about a month in order to minimize the effects of experience and memory of stimulation. Patients are then randomized to either the DBS group that receives active stimulation programmed to the settings found to be optimal during titration in phase IV, or to the sham group that receives 0 V (no electrical current) stimulation. As a technical detail, for minimizing risk to blinding procedures, the pulse generator is always kept on during all phases so that if any patients have tests that could indicate the status of the generator, it will always appear to be turned on Patients are randomized in a 1:1 ratio to one of the two groups.

#### Phase VI: open-label phase

Upon completion of the third month post-crossover, all patients are reprogrammed to the optimized stimulation settings, as deemed necessary by the investigators at that time to maximize clinical benefits. There is no sham stimulation after this point. The goal is to reduce pain-related disability. Follow-up assessment of outcomes is conducted at month 9, 12, 18 and 24.

### Endpoints of safety

Risks can be related to the procedures for implantation of DBS hardware, or the stimulation of the target area. Additional risks could be related to conducting MRI with implanted DBS. Events or instances that can present as risks are noted in detail in Table 2. Clinical experience of the research team, pre-operative image guidance, prophylactic antibiotics, and preparatory laboratory work is critical in mitigating risks related to DBS and implantation. Risks of stimulation are mitigated by choosing settings below the threshold for intolerable side effects [19]. Risk for suicidal ideation is monitored throughout the trial using C-SSRS. The protocol is outlined such that if serious signs are detected, psychiatric assessment will promptly follow. If the risk remains high for more than 28 days or if two or more events of imminent risk are recorded, then the individual will be removed from the blinded phase of the study.

**Table 2 T2:** Overall risks of the study across various categories

**Category of Risks**	**Specific Risks**
**Risks of DBS surgery and Implantation of Pulse Generator**	Intracerebral hemorrhage; infection abscess; meningitis; misplacement of leads requiring revisions; post-operative displacement of leads; reaction to lead materials; hypodensity with mass effect around lead; intracranial extra-axial hemorrhage; stroke; pain at site of surgery; migration of leads; erosion of skin over hardware; hardware problems, such as abnormal impedances; hydrocephalus; seizures/epilepsy; cerebrospinal fluid leak; seroma; collection formation; pneumothorax/hemothorax/pleural effusions due to IPG; injury along the tunneling trajectory in the region of head, neck or chest; risks related to anesthesia (severe injury, cognitive decline, and death)
**Risks Pertaining to Hardware Maintenance**	Migration; infection; hardware malfunction/break; insulation problems; leaks of electricity; reaction to implants; erosion; incompatibility with MRIs; incompatibility with surgical equipment, medical devices or diagnostic devices
**Risks due to stimulation and conduct of the experiment**	Stroke/brain hemorrhage; dizziness; dyspraxia, dystonia, facial and limb muscle weakness, abnormal voluntary movements; numbness; attention, memory or language processing difficulties; suicide ideation and imminent risk of suicide (based on MADRS’ item 10, CSSRS’ item 5, BDI’s item 9 and behavioral interview); hypomania or motor contractions; any other unanticipated neurological deficits; worsening of chronic pain condition; behavioral or cognitive changes; rebound of symptoms when stimulation is stopped; visual field defects or eye movement disorders; headache; abnormal thinking; behavioral or psychiatric problems; changes in sexual function; disorders of consciousness; cardiovascular or respiratory events; electromagnetic interference; MRI may damage implantable devices
**Risks Involved with Imaging**	MRI may cause lesion to region targeted by DBS; fatigue and discomfort associated with nociceptive stimuli

IPG, implantable pulse generator; MADRS, Montgomery-Asburg Depression Rating Scale; C-SSRS, Columbia Suicide Severity Rating Scale; BDI, Beck Depression Inventory; MRI, Magnetic Resonance Imaging.

### Feasibility of blinding

Our current trial is a double-blinded study where neither patients nor investigators performing outcome assessments know whether DBS or sham is delivered. Maintaining a blinded study is important because of the subjective nature of reports of pain and disability. Loss of blinding may occur due to the magnitude of the therapeutic effect or any other subjective perception that indicates that active DBS or sham is delivered. Safeguards have been incorporated to prevent loss of experimental blinding; for instance, stimulation is turned to 0 V after the programming and titration in phase IV to minimize the chance of memory of stimulation affecting the patient’s perception of receiving active DBS or sham in blinded phase V. In addition, patients and blinded investigators are asked separately via questionnaire, what they believe is the status of the stimulation (active or sham). At the end of the study, we will evaluate how effective the blinding strategy was in order to guide us forward.

